### 8.2 Cost effectiveness analysis (CEA)

#### GENERAL CONSIDERATIONS CEA

The aim of the economic evaluation is to relate the difference in societal and healthcare costs between procedural sedation and general anesthesia to the difference in clinical effects. Both a cost-effectiveness and cost-utility analysis will be performed with a time horizon of 12 months. Thus, discounting is not necessary.

#### COST ANALYSIS CEA

Costs will be measured from a societal perspective using internet questionnaires based on the iMCQ after 6 weeks, 3, 6 and 12 months of follow-up. Direct costs include costs of primary and secondary care, complementary care and home care. Indirect costs include absenteeism from paid and unpaid work, and presenteeism. The friction cost approach will be used to estimate indirect costs. For the valuation of health care utilization standard prices published in the Dutch costing guidelines [34] will be used.

Medication use will be valued using prices of the Royal Dutch Society for Pharmacy [35].

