## SUMMARY

**Rationale:** Hysteroscopic myomectomies are performed in the majority of Dutch hospitals. The number of procedures for submucosal type 0 or I myomas between 1-3 cm performed in the operating room is estimated to be 3000 per year. Hysteroscopic myomectomy is currently performed in daycare under general anesthesia. A considerable cost reduction is expected when procedural sedation (PSA) is applied. The major contributing factors to the cost reduction are the shift from surgery in an operating theatre to an office-based setting, shorter hospital stay and outpatient care versus day care. We expect higher patient satisfaction, as hospital stay is shorter and side effects such as nausea are reduced. However, both safety and effectiveness – including the necessity for re-intervention due to incomplete resection – have not yet been fully evaluated.

**Objective:** Is hysteroscopic resection of submucous myomas under procedural sedation with propofol (PSA) in an outpatient setting a cost-effective alternative for hysteroscopic myomectomy performed under general anesthesia in the operation room?

**Study design:** non-inferiority, multicenter RCT, with a cost effectiveness analysis (CEA) alongside it.

**Study population:** patients with submucosal type 0 or I myomas (FIGO (PALM COEIN)) with a maximum diameter of 3 cm. We use a non-inferiority design: based on estimated risk of 2,5% incomplete resections in both groups, with an non-inferiority upper limit of 10%, 205 women are needed.

**Intervention:** hysteroscopic resection of submucous myomas under procedural sedation with propofol, compared to general anesthesia

**Main study parameters/endpoints:** 1) complete resection 2) costs, pain, menstrual blood loss (PBAC score), , quality of life, return to daily activities/work, hospitalization, (post)operative complications, re-interventions.

**Nature and extent of the burden and risks associated with participation, benefit and group relatedness:** Patients participating in this study are requested to complete a questionnaire at baseline, after 24 hours, 2 weeks, 8 weeks, 6 months and 12 months after the procedure. At 6 weeks after the procedure patients are asked to visit the outpatient department for a transvaginal ultrasound to assess the completeness of resection. This visit is part of the current usual care.

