### **Questionnaires**

Participating women will fill in questionnaires at baseline, which will be given before the surgical procedure. During follow-up, patients will fill in questionnaires at 24 hours, 2 weeks, 8 weeks, 6 and 12 months after randomisation. Questionnaires will contain:

- Short questionnaire on side effects 24 hours after surgery.
- the EuroQoL (EQ-5D-5L) questionnaire (15 questions) to assess the quality of life
- PBAC scores to assess the amount of menstrual blood loss
- Uterine Fibroid Symptoms – Quality of Life (UFS-QoL) questionnaire (37 questions) to assess the quality of life focussing on patients suffering from uterine fibroids
- Recovery Index (RI-10) questionnaire (10 questions): to assess the patients' recovery process

- Medical Consumption Questionnaire (iMCQ)[32]: for cost effectiveness analysis
- Productivity Cost Questionnaire (iPCQ)[33] to assess productivity loss
- Short questionnaire on recurrence and re-interventions at 12 months after surgery.

|           | Side effects
Pain
(VAS) | EQ-5D-5L | PBAC | UFS-QoL | RI-10 | iMCQ | iPCQ | Re-intervention |
|-----------|-------------------------------|----------|------|---------|-------|------|------|-----------------|
| Baseline  |                               | X        | X    | X       |       |      |      |                 |
| 24 hours  | X                             | X        |      |         | X     |      |      |                 |
| 2 weeks   |                               | X        |      |         | X     |      |      |                 |
| 8 weeks   |                               | X        | X    | X       | X     | X    | X    |                 |
| 6 months  |                               |          |      |         |       | X    |      |                 |
| 12 months |                               | X        | X    | X       |       | X    |      | X               |

A patient preference study (for which a different study protocol will be created) will be conducted alongside the trial including evaluation of patient satisfaction.

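### The cost time points in Section 8.2 do not match the questionnaire schedule in Section 6.3, and productivity loss is scheduled only once, at 8 weeks, for a 12-month societal analysis

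*Protocol*

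**What the plan says.** The horizon is set in Section 8.2, General considerations: "Both a cost-effectiveness and cost-utility analysis will be performed with a time horizon of 12 months". Under Cost analysis, the same section takes a societal perspective and collects costs "using internet questionnaires based on the iMCQ after 6 weeks, 3, 6 and 12 months of follow-up". It defines the indirect part: "Indirect costs include absenteeism from paid and unpaid work, and presenteeism". Missing cost and effect data are to be multiply imputed, and QALYs come from the EQ-5D-5L.

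The data collection is set in Section 6.3, Questionnaires: "patients will fill in questionnaires at 24 hours, 2 weeks, 8 weeks, 6 and 12 months after randomisation". The Summary gives the same follow-up times: "complete a questionnaire at baseline, after 24 hours, 2 weeks, 8 weeks, 6 months and 12 months after the procedure". (The two count from different origins, randomisation and procedure.) Section 6.3 lists the iMCQ for the cost-effectiveness analysis and, as a separate instrument, the "Productivity Cost Questionnaire (iPCQ)[33] to assess productivity loss". The schedule table marks:

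- iMCQ at 8 weeks, 6 months and 12 months;
- iPCQ at 8 weeks only;
- EQ-5D-5L at baseline, 24 hours, 2 weeks, 8 weeks and 12 months;
- re-interventions at 12 months.

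**The concern.** Two sections of one protocol give different data collection for the same analysis, and the schedule is the one that determines which forms patients receive. If it is followed, the indirect-cost part of a 12-month societal total rests on one early questionnaire.

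The period left out matters for this comparison. Completeness of resection is judged by ultrasound at 6 weeks, so work loss from a re-intervention prompted by that scan would largely fall after the only iPCQ. The Summary and Section 1 say that re-intervention due to incomplete resection has not yet been fully evaluated. If sedation led to more incomplete resections, the re-intervention would be recorded and its medical cost could be picked up by the later iMCQ. The accompanying absence from work would not be, and the societal comparison would lean towards sedation.

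The gap also carries forward. The budget impact analysis in Section 8.3 takes its resource-use rates from this evaluation and reports costs per year over 5 years, with productivity losses as one component. An analysis plan written later cannot recover answers that were never requested.

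**Working it through.** **1. The plan's own saving figure.** Inputs from Section 1, Anticipated cost-effectiveness: 3000 procedures a year, EUR 595 saved per resection, about EUR 2.8 million societal saving a year.

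- Healthcare saving: 3000 × 595 = EUR 1,785,000, which agrees with the stated figure of almost 1.8 million.
- Societal saving per woman: 2,800,000 / 3000 = EUR 933.
- Productivity component: 933 − 595 = EUR 338, and 338 / 933 = 36%.
- The 2.8 million is rounded. A range of 2.75 to 2.85 million gives EUR 322 to 355.

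This shows that productivity is a material component of the forecast. It does not size what is lost after week 8 (see the objection).

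**2. Cost time points side by side.**

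| Time | Costs per Section 8.2 | iMCQ in 6.3 | iPCQ in 6.3 | EQ-5D-5L in 6.3 |
|---|---|---|---|---|
| 6 weeks | yes | no form | no form | no form |
| 8 weeks | no | yes | yes | yes |
| 3 months | yes | no form | no form | no form |
| 6 months | yes | yes | no | no |
| 12 months | yes | yes | no | yes |

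Two of the four times in Section 8.2 (6 weeks, 3 months) have no questionnaire. The other two agree for the iMCQ. The scheduled 8-week form is absent from Section 8.2. The 6-week contact is the ultrasound visit.

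**3. Productivity coverage.** Taking 12 months as 52 weeks and letting the 8-week iPCQ cover everything up to week 8: (52 − 8) / 52 = 44 / 52 = 85% of the horizon without a scheduled productivity measurement. The protocol gives no recall period for the iPCQ.

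**4. How many women could be affected.** Section 4.4 assumes 2.5% incomplete resections in both arms and a margin of 7.5 percentage points.

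- At the planning assumption: 0.025 × 205 = about 5 women in total, with no expected difference between arms.
- At the margin: 0.075 × 205/2 = 7.7, so about 8 more women with an incomplete resection under sedation (dropout ignored).

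These are counts of incomplete resections. The protocol does not say how many would lead to a re-intervention or how much work each would cost, so no euro figure follows.

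**5. QALYs.** With EQ-5D-5L at 0, 24 hours, 2, 8 and 52 weeks, the trapezoid weights of the last two values are:

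- 8 weeks: (6 + 44) / 2 / 52 = 25 / 52 = 48%;
- 12 months: 44 / 2 / 52 = 22 / 52 = 42%.

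A 12-month QALY can therefore be computed, with 44 of 52 weeks on one straight line. If the true 6-month utility lies x off that line, the QALY changes by (18 + 26) / 2 / 52 × x = 0.423x. For an assumed x of 0.01 to 0.10 that is 0.004 to 0.042 QALY. It biases the comparison only if the arms deviate differently. With a 6-month value added, the longest gap falls to 26 weeks and the weights become 12/52 = 23% (8 weeks), 22/52 = 42% (6 months) and 13/52 = 25% (12 months).

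**The case against.** **Section 8.2 does plan costs to 12 months.** Read alone, it collects societal costs, indirect costs included, with iMCQ-based forms up to a year, and those forms might carry productivity items. This stands in part: the protocol contradicts itself and does not show which section is intended, so the loss of data is conditional on the schedule being followed. But Section 6.3 assigns productivity loss to the iPCQ, separately from the iMCQ, and marks it once. The reconciliation is needed on either reading.

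**Most of the expected work loss is early.** Section 1 ties the further societal saving to quicker return to normal activities and shorter absence from work, which is the period an 8-week iPCQ addresses. At the planning assumption only about 5 women would have an incomplete resection, with no expected arm difference. This stands as an argument about size. A reader might infer from the 36% that more than a third of the societal result goes unmeasured. The protocol does not support that: EUR 338 is the whole forecast productivity component, and much of it may fall before week 8. If early loss is all that is intended, the analysis should say so.

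**The EQ-5D-5L timing is defensible.** Nothing in the protocol requires a 6-month value, the surgery is the same in both arms, and the expected benefit is in early recovery. This stands. The missing 6-month EQ-5D-5L is a weakness of precision in the QALY, not an error.

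**Cost-effectiveness is a secondary objective in Section 2.** True, although the Summary frames the whole trial question as one of cost-effectiveness.

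**Conclusion.** The point holds for the cost time points and for indirect costs. Sections 6.3 and 8.2 disagree on when costs are measured. As scheduled, productivity loss is measured once, at 8 weeks, for an analysis that claims a societal perspective over 12 months. About 85% of the horizon has no scheduled productivity data, assuming that the 8-week form reaches back to the start of the horizon and that both are counted from the same origin. The resulting cost error cannot be derived from the protocol. Its direction would favour sedation only if sedation led to more late work loss.

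A reader might go further and infer that the 12-month economic evaluation as a whole cannot be built. The protocol does not support this. Direct costs have the iMCQ at 8 weeks, 6 and 12 months, although full coverage depends on recall periods that are not stated. QALYs can be computed from the five EQ-5D-5L times. The primary endpoint and the sample size of 205 are not affected.

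**What to change.** 1. Reconcile Sections 6.3 and 8.2 so that both give the same cost time points, counted from one stated origin. If the 6-week and 3-month times are kept, forms for them must be added to the schedule. If not, Section 8.2 must be corrected.
2. Add the iPCQ to the 6- and 12-month questionnaires that already go out, and state the period that each administration covers.
3. If the iPCQ is not added, label productivity costs as covering up to 8 weeks only, in Section 8.2 and in the budget impact analysis, and do not present them as a full 12-month societal total. Twelve-month healthcare costs can still be reported.
4. Optional: add the EQ-5D-5L to the existing 6-month questionnaire, which cuts the longest interpolation from 44 to 26 weeks.

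The cost of items 2 and 4 is a few more questions for patients on existing online forms. Items 1 and 3 are wording, unless extra 6-week and 3-month forms are chosen, which would add patient burden. The change to the forms helps only women who have not yet passed the time points concerned.

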## PATIENT OUTCOME ANALYSIS CEA

Societal costs will be related to the following effect measures in the economic evaluation:

- 1) % of complete resection;
- 2) quality-adjusted life-years (QALYs) based on the Dutch tariff for the EuroQol (EQ-5D-5L) [36-37].

The analysis will be done according to the intention-to-treat principle. Missing cost and effect data will be imputed using multiple imputation. Incremental cost-effectiveness ratios (ICERs) will be calculated by dividing the difference in mean total costs between the treatment groups by the difference in mean effects. Bootstrapping with 5000 replications will be used to estimate 95% confidence intervals around cost differences and the uncertainty surrounding the ICERs. Uncertainty surrounding the ICERs will be graphically presented on cost-effectiveness planes. Cost-effectiveness acceptability curves showing the probability that the intervention is cost-effective in comparison with usual care for a range of different ceiling ratios will also be estimated [38]. Adjustment for confounders and effect modifiers will be done if necessary.

### **8.3 Budget Impact Analysis (BIA)**

#### GENERAL CONSIDERATIONS BIA

The budget impact analysis will be performed based on the recommendations from Sullivan et al [39]. In the budget impact analysis, the effectiveness of the treatments will be extrapolated over a period of 5 years based on the estimates obtained from the proposed study. Perspectives that will be considered are the societal, government (Budget Kader Zorg) and insurer perspective. Different implementation scenarios (ranging from 0% to 100% implementation) will be evaluated.

#### COST ANALYSIS BIA

The total number of patients eligible for the intervention will be estimated based on Dutch epidemiological data. Resource utilization is calculated by multiplying the number of eligible patients with the resource utilization rates obtained from the economic evaluation. Different prices will be used to value resource use depending on the perspective of the analysis: Dutch standard costs for the societal perspective, actual NZA tariffs for the government perspective, and average tariffs NZA for the insurer perspective. Both resource use and annual costs will be presented over a 5 year period for all perspectives. Aggregated and disaggregated (e.g. GP care, secondary care, and productivity losses) total costs per year will be presented for the different perspectives and scenarios.

#### **8.4 Interim analysis**

Given the low risk of adverse events, an interim analysis will not be planned.

## **9. ETHICAL CONSIDERATIONS**

### **9.1 Regulation statement**

The study will be conducted according to the principles of the Declaration of Helsinki (WORLD MEDICAL ASSOCIATION DECLARATION OF HELSINKI Ethical Principles for Medical Research Involving Human Subjects, Version Fortaleza, Brazil, October 2013,) and in accordance with the Medical Research Involving Human Subjects Act (WMO).

### **9.2 Recruitment and consent**

The gynaecologist participating in the network will inform the patient about the study and refer the patients to dedicated research nurses. These nurses will counsel patients, ask for informed consent, and perform randomisation. The research nurse will organize the required treatments, depending on the result of the randomisation.

### **9.3 Benefits and risks assessment, group relatedness**

This study will not impose extra risk on women participating in the trial, since it compares anesthetic procedures that are all used in daily practice. Hysteroscopic myomectomy is performed in a similar way regardless of the type of anesthesia that is applied. Hysteroscopic myomectomy using procedural sedation is expected to be equally effective as under general anesthesia. A significant cost reduction is expected, whilst patient satisfaction/preference is comparable or increased. Therefore research in order to optimize treatment is necessary.

### **9.4 Compensation for injury**

The Máxima Medical Centre has an insurance which is in accordance with the legal requirements in the Netherlands (Article 7 WMO). This insurance provides cover for damage to research subjects through injury or death caused by the study.

The insurance applies to the damage that becomes apparent during the study or within 4 years after the end of the study.

## **10. ADMINISTRATIVE ASPECTS, MONITORING AND PUBLICATION**

### **10.1 Handling and storage of data and documents**

Data will be collected using a website dedicated to studies in the Dutch Consortium for women's health and reproductivity studies ([www.studies-obsgyn.nl](http://www.studies-obsgyn.nl)). Similar website oriented databases have already been developed.

Data monitoring will be done by research nurses in each of the participating centres. A substantial part of these research nurses is already working for the above mentioned consortium. Participants will be given a computer generated numeric code. Data handling will be done anonymously, with the patient code only available to the local investigator and the research nurse working in the local centre.

In accordance with guidelines of the Dutch Federation of University Medical Centers (NFU) the data will be kept for 15 years.

### **10.2 Amendments**

Amendments are changes made to the research after a favourable opinion by the accredited METC has been given. All amendments will be notified to the METC that gave a favourable opinion.

Non-substantial amendments will not be notified to the accredited METC and the competent authority, but will be recorded and filed by the sponsor.

### **10.3 Annual progress report**

The sponsor/investigator will submit a summary of the progress of the trial to the accredited METC once a year. Information will be provided on the date of inclusion of the first subject, numbers of subjects included and numbers of subjects that have completed the trial, serious adverse events/ serious adverse reactions, other problems, and amendments.

### **10.4 End of study report**

The investigator will notify the accredited METC of the end of the study within a period of 8 weeks. The end of the study is defined as the last patient's last visit.

In case the study is ended prematurely, the investigator will notify the accredited METC within 15 days, including the reasons for the premature termination.

Within one year after the end of the study, the investigator/sponsor will submit a final study report with the results of the study, including any publications/abstracts of the study,

to the accredited METC.

#### **10.5 Public disclosure and publication policy**

The principal investigator will publish the results of the study in a peer reviewed medical journal as soon as appropriate.

